**Fig. 2 Fig2:**
[figure not shown]
Adapted framework for the prediction of risky behaviour in adolescents (adapted from Wiers et al., 2010; © 2010 Wiers, Ames, Hofmann, Krank and Stacey)

Like the ProWISE intervention, conversational style of the TIPs is designed in an MI congruent way. As central mechanisms of action, the TIPs are designed to increase self-monitoring and promote awareness of potential discrepancies between drinking intentions and actual consumption, thereby raising the awareness of ambivalence as an important mechanism in the development of a motivation to change according to MI theory [44]. According to a recent study, 40% of adolescents and young adults (aged 16–25 years) consume alcohol heavily despite they intent not to [48]. Individualised feedback on this discrepancy embedded in real-life context was found to be effective in reducing heavy drinking [33]. Furthermore, content of the TIPs draws on elements of MI theory by highlighting participants’ responsibility for change and freedom of choice, by providing information on harm-reduction and drink-less strategies as well as by providing feedback on alcohol use and by promoting self-efficacy for the achievement of low-risk alcohol use or abstinence.

Phase 2 of the TIP development will include pilot testing of feasibility and acceptability of the TIPs with *N* = 20 adolescents of the target population of ≥ 12- year-olds with risky alcohol consumption. Two focus groups (*n* = 5 each) will additionally provide feedback on content and conversational style of the TIPs, which will be adapted accordingly.

### Control conditions

Participants in the control groups will receive either: (1) the ProWISE intervention plus weekly TA of alcohol use for 12 weeks every Sunday (ProWISE-TA); or (2) the ProWISE intervention only; or (3) web-based psychoeducation on alcohol use in childhood and adolescence (control). The psychoeducation control group is included in this study in order to test if findings from the previous evaluation of the ProWISE intervention can be replicated, since the intervention has been refined for the current study. Previously, the ProWISE intervention was tested as a self-help program (1) without school-based screening and referral to intervention, (2) in a different age group (16–18 years), and (3) in a slightly different population of at-risk drinkers (i.e. not excluding children and adolescents with AUDIT scores ≥ 20). The ProWISE-TA condition is included in the study design in order to differentiate effects of the TIPs from assessment reactivity [49].

### Data collection

Participants will complete school-based online assessments at time of enrolment in the CP (t_0_) as well as at one and two years after enrolment (t_5_, t_6_) (Fig. 3). SP-specific assessments will be administered following enrolment in the SP (t_1_) and at the SP-specific follow-ups at three (t_2_), six (t_3_) and nine (t_4_) months after enrolment in SP3. All data will be collected online via central servers that are used for both the school-based assessments and the different interventions that are conducted via the ProHEAD online platform. Data will be handled in accordance with German legal regulations concerning data protection and data security (Data Protection Law of the Federal State of Baden-Wuerttemberg, Data Protection Law of the Free and Hanseatic City of Hamburg and German National Data Protection Laws) as well as EU General Data Protection Regulation. Data storage and transfer will be encrypted. All follow-up assessments will be conducted online via a password-secured website and will be recorded in the individual case report forms (CRF). An independent Data and Safety Monitoring Committee (DSMB) will oversee all aspects of data collection, handling and analysis. The DSMB will comprise independent researchers with expertise in research methodology, child and adolescent mental health, and technology-based alcohol interventions. Members of the DSMB will have their first meeting before inclusion of the first study participant.

**Fig. 3 Fig3:**
[figure not shown]
Schedule of enrolment, assessment and intervention. *Note:*
*CP* central project, *SP3* sub-project 3, *ProWISE* single-session web-based brief motivational alcohol intervention, *PE* psychoeducation, *TA* text-message-initiated assessment, *TIP* text-message-initiated individualised prompt, *CRAFFT-d* screen for risky alcohol use (Car, Relax, Alone, Forget, Friends, Trouble), *AUDIT* Alcohol Use Disorders Identification Test, *Adapted AUDIT-C (30d)* Alcohol Use Disorders Identification Test - Consumption adapted to assess alcohol use in the past 30 days, *RAPI* Rutgers Alcohol Problem Index, *RTC* Algorithm Readiness to change drinking algorithm, *DMQ-R SF* Drinking Motive Questionnaire-Revised Short Form, *AHSQ* Actual Help-Seeking Questionnaire, *SDQ* Strengths and Difficulties Questionnaire, *KIDSCREEN-10* Quality of life measure for children and adolescents, *CAST* Cannabis Abuse Screening Test, *SCL-9-K* Short version of the Symptom Checklist, *SCS-K-D* German short form of the Self-Control Scale, *AIC* Adolescent Injury Checklist

### Measures

Sociodemographic data [50] will be assessed as part of the school-based online assessment. Measures assessed for the CP and the other SPs are described elsewhere [36–39]. The CRAFFT-d screening test for risky alcohol use in adolescence in its validated German version [40] will be applied as part of the school-based screening to identify children and adolescents with at-risk alcohol use which will be included in the ProWISE-TIP trial. This six-item questionnaire assesses alcohol-related risk behaviours applying a binary yes/no response format (e.g. ‘Do you ever use alcohol to relax, feel better about yourself, or fit in?’; ‘Do you ever use alcohol while you are by yourself?’). Two or more positive answers indicate risky alcohol use. The CRAFFT-d is validated in the age group of adolescents aged 12–18 years [40].

Drinking motives required for individualisation of the TIPs will be assessed by the Drinking Motive Questionnaire Revised Short Form (DMQ-R SF) [46]. This youth-specific self-report questionnaire comprises 12 items assessing the frequency (never / rarely / sometimes / often / always) of different motives for drinking in the past 12 months (‘In the last 12 months, how often did you drink…’). Three items each represent the four drinking motives enhancement (e.g. ‘…because it’s fun?’), social (e.g. ‘…because it helps you enjoy a party?’), conformity (e.g. ‘…to fit in with a group you like?’) and coping (e.g. ‘...to forget about your problems?’). Scores for drinking motives are calculated by mean sum scores of the items representing the respective drinking motive with higher scores representing more predominant motives. The DMQ-R SF is validated in the age group 12–18 [46].

#### Primary outcome measure

For reasons of comparability, we chose to use the same primary outcome as in our previous study, testing the effectiveness of the original version of the web-based brief alcohol intervention without TIPs [24]. Therefore, the primary outcome is alcohol use in the past 30 days at nine-month follow-up as assessed by an index score for frequency and quantity of drinking and frequency of binge drinking calculated from the first three items of the Alcohol Use Disorders Identification Test (AUDIT-C) [41] adapted to assess drinking in the past 30 days. Frequency of alcohol consumption and frequency of having six drinks at one occasion (binge drinking) are assessed with response options ranging from 0 (never) to 4 (four or more times a week). The assessment of quantity of standard drinks consumed per typical drinking occasion (0 = one or two to 4 = ten or more) is supported by a graphical overview over units of alcoholic drinks defined as standard drinks. The AUDIT-C is validated in a sample of 14- to 18-year-old students in Germany [51].

#### Secondary outcome measures

As secondary outcomes, alcohol-related problems will be assessed by a brief version of the Rutgers Alcohol Problem Index (brief RAPI) [52], a youth-specific measure for alcohol-related problems at the SP-specific follow-ups. Participants are asked 16 questions about the frequency of experiencing different situations in the past three months while they were drinking alcohol or as a result of their alcohol use (e.g. ‘Not able to do your homework or study for a test’; ‘Got into fights with other people (friends, relatives, strangers)’; ‘Wanted to stop drinking but you couldn’t’). Response options range from ‘never’, ‘1–2 times’, ‘3–5 times’, ‘6–10 times’ to ‘more than 10 times’. Higher sum scores indicate more severe alcohol-related problems. The brief RAPI was validated in a sample of 12- to 18-year-olds [52]. Alcohol-related injuries in the past six months will be assessed by a modified version of the Adolescent Injury Checklist (AIC) [53]. Prevalence of experiencing nine different injuries while or shortly after consuming alcohol are assessed (e.g. ‘In the past 6 months, were you injured while or shortly after drinking alcohol … by being in a physical fight with someone? / ... by falling? / ... while riding in a car, truck or bus?’). Response options are ‘yes = 1 / no = 0’ with a higher sum score indicating higher prevalence of alcohol-related injuries in the past six months. Alcohol-related sexually risky behaviour will be recorded by assessing the frequency of experiencing six different risk situations while drinking or shortly after drinking alcohol (e.g. ‘I was sexually harassed’, ‘I had sex, which I couldn’t fully remember later on’). Co-occurring substance use will be assessed as a secondary outcome by the 30-day prevalence of cannabis and other illegal drug use. Additionally, readiness to change alcohol use will be assessed using the Brief Readiness to Change Drinking Algorithm as proposed by Epler et al. [54]. The algorithm comprises three items allowing to categorise risky drinkers’ motivation to change into the stages ‘pre-contemplation’, ‘contemplation’ and ‘action’ according to the Transtheoretical Model of Behaviour Change [55]. Response options for items vary (e.g. ‘Has the amount you drink changed in the past 3 months? Yes, I drink less / Yes, I drink more / No, I drink the same’) and allow allocation of the respondent to one of the three stages of change as described above. The Brief Readiness to Change Drinking Algorithm was validated in an adult population [54].

Additional secondary outcomes will be assessed in the school-based follow-ups at one and two years after enrolment. Help-seeking will be assessed using an adapted version of the Actual Help-Seeking Questionnaire (AHSQ) [56], which assesses actual help-seeking behaviour by listing potential help sources and measuring whether help has been sought from the respective sources within a specified time-period for a specified problem. The 13-item questionnaire comprises three subscales: whether informal help has been sought; whether formal help has been sought; and whether no help has been sought. Response options are 0 = ‘no’, 1 = ‘yes, in the past 12 months’ and 2 = ‘yes, but longer ago then 12 months’. The Actual Help-Seeking Questionnaire (AHSQ) is validated in a sample of 16- to 19-year-old students [56]. Mental health symptoms will be assessed using the Strengths and Difficulties Questionnaire (SDQ), a self-report screening questionnaire for children and adolescents aged 2–17 years [42]. The four subscales (emotional, conduct, hyperactivity and peer problems), each scored on a scale of 0–10, will be assessed. Higher scores indicate a higher level of psychopathology. Quality of life will be assessed using the KIDSCREEN-10 [57]. The KIDSCREEN is an international cross-culturally comparable quality-of-life assessment instrument validated for children and adolescents aged 8–18 years. The KIDSCREEN-10 index comprises 10 items, which provide a global measure of health-related quality of life. Items are answered on a 5-point response scale and are coded in a way that higher values indicate better quality of life. Furthermore, program usage patterns (frequency of replies to TIPs, duration, completion) based on log-file data will be analysed.

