## Methods/Design

### Design

The ProWISE-TIP trial is a sub-project (SP) of the multisite, prospective ProHEAD consortium. The aim of ProHEAD is the development, implementation and evaluation of Internet-based programs promoting mental health in healthy children and adolescents, preventing mental health problems (depression, eating disorders, risky alcohol use) in those who are at high risk and enhancing help-seeking of children and adolescents with mental health problems [36]. The ProHEAD consortium aims to improve access to prevention and care for young people aged ≥ 12 years by capitalising on novel E-health tools. For a detailed description of the ProHEAD consortium design, please refer to Kaess et al. [36]; for details on the other SPs, please refer to the respective study protocols in this issue [37–39].

Effectiveness of the ProWISE-TIP intervention will be tested in a four-armed, randomised controlled design with observer blinded group allocation with trial conditions: (A) ProWISE plus TIP for 12 weeks (ProWISE-TIP); (B) ProWISE plus text-message-initiated assessment (TA) for 12 weeks (ProWISE-TA); (C) ProWISE intervention only (ProWISE only); and (D) web-based psychoeducation on alcohol use in childhood and adolescence (control group). Participants will be followed up at three, six and nine months after enrolment in the SP and at one and two years after enrolment in the central project (ProHEAD consortium) (Fig. 1). A schedule of enrolment, assessment and intervention is provided in Fig. 3 and a populated Standard Protocol Items: Recommendations for Interventions Trials (SPIRIT) Checklist is provided in Additional file 1.

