### Recruitment and randomisation

Participants for the trial will be recruited through the ProHEAD infrastructure with five centres (Heidelberg, Hamburg, Leipzig, Marburg, Schwäbisch Gmünd) actively recruiting and drawing children and adolescents from a national school-based sample. For a detailed description of the recruitment process, please refer to Kaess et al. [36]. After enrolment in the central project, study participants will be allocated to one of the five SPs according to their screening result (Fig. 1). All participants receive an e-mail containing a link to an encrypted webpage where they can register to the respective SP. Participants with a positive screening for at-risk alcohol use are invited to take part in the ProWISE-TIP trial and referred to the SP-specific online baseline assessment (Fig. 3). After completion of the assessment, participants will be randomised to one of the four study arms (A) ProWISE plus TIP for 12 weeks (ProWISE-TIP); (B) ProWISE plus TA for 12 weeks (ProWISE-TA); (C) ProWISE intervention only (ProWISE only); (D) web-based psychoeducation on alcohol use in childhood and adolescence (control group). Randomisation is conducted automatically by the computer program on the basis of predefined lists and following a permutated block design. Randomisation will be stratified by age and gender. Once participants have completed the trial-specific online baseline assessment, they automatically receive a computer-generated e-mail containing a link to access the online content in their respective trial condition.

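### The injury checklist's six-month recall does not fit follow-ups three months apart: if it is given at each visit, about half of the three-month window precedes randomisation and adjacent windows overlap

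*Protocol article*

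**What the plan says.** All references are to the protocol article.

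- **Recall period.** Secondary outcome measures: "Alcohol-related injuries in the past six months will be assessed by a modified version of the Adolescent Injury Checklist (AIC"). The sample item has the same time frame: "In the past 6 months, were you injured while or shortly after drinking alcohol". Nine injury types are answered yes or no and summed.
- **Visit times.** Design: "Participants will be followed up at three, six and nine months after enrolment in the SP". Data collection gives the same three times.
- **Start of the clock.** Recruitment and randomisation places allocation directly after the trial-specific baseline assessment: "After completion of the assessment, participants will be randomised to one of the four study arms". Randomisation is therefore at about month 0.
- **Comparison measure.** The brief RAPI, described just before the injury checklist and tied expressly to the trial-specific follow-ups, asks about the "frequency of experiencing different situations in the past three months".
- **Visits for the checklist.** The sentence on injuries names none. The injury outcome stands with the outcomes of the trial-specific follow-ups. The outcomes for the one- and two-year school assessments come afterwards and are introduced as additional.
- **Role.** Statistical analysis makes the secondary endpoints exploratory.

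**The concern.** A recall period longer than the gap between visits has two effects. At the first follow-up it reaches back before randomisation, so the score includes injuries that no intervention could have prevented. At later follow-ups, adjacent windows share time. The items are yes/no and the description mentions no dating of injuries, so the same injury can score at two visits and cannot be assigned to one period.

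The abstract and the aims name reduced alcohol-related harm as a purpose of the trial. The background cites a lower prevalence of alcohol-related injury in an earlier text-message trial as support for the approach. A score that mixes in pre-randomisation time is less able to show such an effect at the visit closest to the 12 weeks of prompts.

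**Working it through.** The plan states no figure to reproduce on this point. The check is arithmetic on intervals.

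**Inputs.** Recall 6 months (Secondary outcome measures); visits at 3, 6 and 9 months (Design, Data collection); randomisation at about month 0 (Recruitment and randomisation); prompts for 12 weeks (Design).

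**Step 1: windows.** At visit t the window is [t - 6, t] months.

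| Visit | Window (months) | Share before randomisation |
|---|---|---|
| 3 months | [-3, 3] | 3/6 = 50% |
| 6 months | [0, 6] | 0% |
| 9 months | [3, 9] | 0% |

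**Step 2: overlaps.** The 3- and 6-month windows share months 0-3. The 6- and 9-month windows share months 3-6, which is 3/6 = half of each. The 3- and 9-month windows share nothing.

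**Step 3: dilution at three months.** With a constant injury rate and a true relative reduction r that applies only after randomisation, the apparent reduction in events is (1 - 0.50) × r. The value r = 30% is an illustration and is not in the protocol. It gives 0.50 × 30% = 15%.

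The halving is exact for event counts and approximate for yes/no items. For one item, assume 0.1 events per three months (also an illustration):

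- Six-month window, no effect: 1 - exp(-0.20) = 18.13%.
- Six-month window, 30% fewer events after randomisation: 1 - exp(-(0.10 + 0.07)) = 15.63%. The apparent reduction is 1 - 15.63/18.13 = 14%.
- Three-month window: 1 - exp(-0.10) = 9.52% against 1 - exp(-0.07) = 6.76%. The apparent reduction is 1 - 6.76/9.52 = 29%.

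**Step 4: dependence on which visits are used.**

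- All three visits: both problems arise.
- Six months only, or baseline and six months: neither arises.
- Six and nine months: overlap only.
- Nine months only: neither arises, and months 0-3 are not observed.

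**Step 5: three-month recall.** The windows become [0, 3], [3, 6] and [6, 9]. There is no pre-randomisation time and no overlap. This is what the brief RAPI already has.

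**Step 6: the nine-month window and the prompts.** Twelve weeks is 84 days, or 84/30.44 = 2.76 months. The nine-month window opens at month 3, which is day 91.3. It contains no prompt time if prompts start within 91.3 - 84 = about 7 days of enrolment. A 14-day delay gives 98 - 91.3 = about 7 days of overlap, and a 28-day delay 112 - 91.3 = about 21 days.

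**The case against.** The strongest objection concerns the premise. No sentence says that the checklist is given at all three visits; the phrase about trial-specific follow-ups belongs to the RAPI sentence. The schedule is in Fig. 3, whose legend lists the checklist but which is not shown here. If the checklist is given only at six months, the problem disappears. This stands, and the point has to be conditional.

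A reader might also infer that the nine-month score is defective because its window falls after the prompt phase. The documents do not support that. The primary outcome, past-30-day use at nine months, also lies wholly after the prompts, and the background cites a 12-week text-message trial that reported injuries at nine months. A three-month recall would place the nine-month window even later, at months 6-9. The absence of overlap also depends on a prompt start within about a week of enrolment.

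A reader might infer that pre-randomisation injuries bias the comparison. They are expected to be balanced by randomisation, so they weaken a difference and favour no arm.

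A further objection is that the mixed repeated-measures model is specified for the primary endpoint only, and no analysis of injury change between visits is stated. This stands: the overlap limits how the six- and nine-month scores may be read, but it does not invalidate a stated analysis. Which visit's score is compared may properly be left to a fuller plan.

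Finally, a shorter recall has a cost. A six-month window at nine months still captures months 3-6 for someone who missed the six-month visit. This is a fair trade-off, but it does not help at the three-month visit.

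**Conclusion.** The point holds conditionally and is of low priority. The six-month recall and the three-month spacing are both stated, and no reason is given for departing from the three-month recall used for the RAPI. If the checklist is given at every trial-specific follow-up, which its placement suggests but the text does not establish, then about 50% of the three-month window precedes randomisation, and an effect confined to the time since randomisation would appear at roughly half its size there. Half of the six-month window is counted again at nine months.

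This rests on randomisation close to enrolment, visits on time and, for the size of the dilution, a constant injury rate. The consequence is reduced sensitivity and double counting in one exploratory secondary outcome. The primary outcome is not affected.

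**What to change.** State the visits at which the injury checklist is given, then take one of two routes.

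1. **Preferred:** change its recall to the past three months at the trial-specific assessments, in line with the brief RAPI.
2. **If six months must stay:** use the six-month visit (months 0-6) as the injury outcome, make no arm comparison at three months, and do not present the six- and nine-month scores as separate periods.

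The first route is a wording change to an online instrument that has already been modified, and Trial status says recruitment has not begun. Its cost is fewer events per visit and less direct comparison with six-month checklist data. Summing the three visits is not a full remedy. The sum would count injury types per window, up to 3 × 9 = 27, and not events. It also needs all three visits: with expected follow-up of 80%, 75% and 70%, at most 70% of participants would have a complete observed sum. The second route needs no change to the instrument but gives up an arm comparison at three months.

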#### Further measures

To measure problematic cannabis use in our sample, we will use the Cannabis Abuse Screening Test (CAST) [58]. The CAST consists of one screening item (to evaluate whether cannabis was used in the last year) and six further questions concerning different aspects of cannabis consumption (e.g. if cannabis was already smoked in the morning). A higher sum value in the CAST indicates a more problematic cannabis use. The CAST is validated in a sample of 14- to 22-year-old youth [58]. Additionally, mental wellbeing in our SP sample will be assessed using a short version of the Symptom Checklist (SCL-K-9) [59], which comprises nine items providing a global severity index for general psychopathology. Respondents are asked to indicate how strongly they have suffered from different symptoms in the past seven days. Response options range from 0 = ‘not at all’ to 4 = ‘very strongly’ with higher scores indicating higher levels of psychopathology. The SCL-K-9 is validated in a sample of 14- to 92-year-olds. In order to control for potential moderators and mediators of intervention effectiveness, we will assess dispositional self-control capacity applying the German short form of the Self-Control Scale (SCS-K-D) [60]. The SCS-K-D consists of 13 items with a five-level response format. A higher total score in the SCS-K-D indicates a higher dispositional self-control capacity. The SCS-K-D is validated in a sample of school children attending tenth grade (mean age = 16.6 years). Furthermore, parental monitoring will be assessed by a validated seven-item questionnaire on adolescents’ perceptions of parents’ monitoring comprising the sub-scales parental knowledge (e.g. ‘my parents/guardian know where I am after school’), youth disclosure (e.g. ‘if I am going to be home late, I tell my parents/guardian’), parental solicitation (‘when I go out, my parents/guardian ask me where I’m going’) and parental control (‘when I go out, my parents/guardian tell me what time I’m going to return’) [61]. The parental monitoring scale was developed for and applied in child and adolescent samples [61, 62].

